## Study Procedure risks

It is expected that adults with symptoms of anxiety will experience clinically significant reductions in the severity of their symptoms. It is also hoped that the techniques taught in the Courses will be applied by participants after the trial is completed, resulting in long term improved management of symptoms. However, because anxiety often develops in teenage hood and early adulthood, it is likely that most of participants will have experienced distressing levels of emotions for several decades. The Course Course encourages them to learn and practice techniques for managing symptoms and, in the short term, this often leads to an increase in levels of symptoms.

Our priority is to support participants to stay safe. Steps for doing this include:

At Application:

Applicants with severe symptoms of depression or suicidal ideation or plan (total score of >23 on the PHQ-9, a reliable and valid measure of the symptoms of depression, and interview by a Psychologist), will not be eligible to participate, and will be provided with written contact details of how to access urgent support and will be strongly encouraged to do so. Applicants assessed as having a principal disorder not targeted by the Courses will not be eligible for this study, as they are unlikely to benefit from the Course. Instead, they will be encouraged to consider other treatment options including accessing their GP or local services, and informed about more appropriate iCBT Courses which may target their specific problem.

During the telephone interview, all applicants are screened for risk of suicide or self-harm. Those at risk will not be eligible to participate, as we believe they require more immediate and intense support than can be provided via the Internet. Instead, they will be assisted to access urgent support from specialist crisis management services and this support will be followed up with written information.

All applicants will also be informed (verbally and in writing) of steps to take if they feel emotionally distressed during the study, including the contact details of the researchers, the importance of contacting their own GP, and contact details of emergency crisis services. Applicants must also provide contact details for their GP or GP Practice, who the MHA Psychologist will only contact if sufficiently concerned about the participant (this is explained to participants verbally, and in the Participant Information Sheet). We do not contact GPs as a standard protocol, as many participants have said that they prefer their participation to remain confidential.

During the Trial, Post-Treatment, and Follow-Ups:

At pre, post-treatment, and at follow-up (2 month), and before each of the 5 lessons, all participants complete a reliable and valid measure of the symptoms and severity of depression (the Patient Health Questionnaire-9 Item; PHQ-9). An increase of 5 or more points is considered an indicator of deterioration, and if this occurs, it will trigger telephone and email contact from the Psychologist. In the event of having contact with a participant who has deteriorated, a Psychologist will make 3 attempts to co-ordinate a telephone assessment to determine risk and develop a management plan. They will also email the participant with details about accessing crisis services.

All participants will also be provided with written information about contact details for emergency services (this information is also included in the footer of all email correspondence), and written details about staying safe in mental health emergencies are included in several locations in the Course materials.

Members of the research team will meet at least weekly to discuss progress. The Chief Investigator will monitor overall progress weekly and will take overall responsibility for this trial.

## Recruitment and screening

Recruitment

Participants will be recruited from MHA consumers over a 2 month period. MHA consumers aged 18-64 years who telephone the [name] Anxiety Support line, will be informed about the aims of the study, and invited to apply. Those interest will be provided with more information and then sent an informed consent form, and asked to complete and return this. Those who complete the form will be telephoned by a Psychologist at the MHA who will provide more details, and administer the Patient Health Questionnaire-9 Item and Generalised Anxiety Disorder-7 item questionnaires. Applicants with scores too high or too low on these questionnaires will be automatically excluded with clear information about where to get treatment, while eligible applicants will be asked to provide demographic details and contact details for their GP.

Participants will be recruited over 2-months, or until 20 people are recruited.

## Informed consent process

Potential applicants are instructed to read the Participant Information Form and then decide whether to complete and return the Consent Form. Additionally, each time a patient logs on to complete a lesson will be taken as a sign of continued consent to participate.

# Safety

## Adverse event reporting

Regular team meetings will be conducted to monitor any difficulties participants may be having and ways of best dealing with these difficulties. Serious adverse events will be reported to the Ethics Committee.

## Serious adverse event reporting

Serious adverse events will be reported to the MQ HREC via SAE documentation and emails. Such information will also be reported to the MHA CEO, [name], and the Centre for Emotional Health Director, [name], and discussed at additional meetings of the researchers.

## Participant safety

Our priority is to support participants to stay safe. Steps for doing this include:

At Application:

Applications with severe symptoms of depression and/or suicidal ideation/plan will not be eligible to participate, and will be provided with written contact details of how to access urgent support and will be strongly encouraged to do so. All applicants will be informed of steps to take if they feel emotionally distressed during the trial, including the contact details of the researchers, the importance of contacting their own GP, and contact details of local emergency services.

During the Trial, Post-Treatment, and Follow-Ups:

During the trial participants will complete a weekly measure of anxiety symptoms (GAD-7) and depression (PHQ-9) to monitor increased levels of either of these symptoms. If symptoms significantly deteriorate or do not improve, the individual will be contacted as soon as possible by the MHA Psychologist.

Significant deterioration in mood or elevated distress triggers protocols involving the MHA Psychologist contacting the participant to discuss their emotional state, and to develop a management plan, which is then documented and followed up as per eCentreClinic policy. The MHA Psychologist is a fully registered Psychologist trained to manage consumers at risk.

Risk will be monitored through the weekly administration of reliable outcome measures which will monitor symptoms of depression and suicidality as well as symptoms of anxiety.

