**Summary**

**Protocol title:** **An open trial of guided iCBT education to determine the benefits of the Wellbeing Course for consumers of the Mental Health Association with symptoms of anxiety**

**Protocol version:** 1.0

**Objectives:** **Primary objectives:** To determine the short and medium term efficacy of the online eCentreClinic Wellbeing Course to MHA consumers, when administered by the MHA.

**Secondary objective:** To determine the acceptability of the online eCentreClinic Wellbeing Course, to MHA consumers.

**Study design:** Open trial design with one group.

**Planned sample size:** The design (see Stat considerations, below) requires a minimum sample size of 15, but 20 will be recruited.

**Selection criteria:** Australian adults aged 18-64 with a principal complaint of symptoms of anxiety (not OCD).

**Study procedure:** Consumers contacted the Mental Health Association (MHA), NSW, telephone support line will be informed about the study. Interested consumers will be sent an Information and Consent Form. Those who return the completed Consent Form will be contacted by an MHA Psychologist who will telephone the applicant and administer a screening questionnaire. Eligible applicants will be sent login codes to access an online education course, designed to help people learn to manage symptoms of anxiety. This evidence-based course, the Wellbeing Course, includes five online lessons and homework assignments, and all participants will receive weekly contact from the MHA Psychologist to provide support and guidance.

Participants will complete questionnaires at pre-treatment, post-treatment, and then at 2 month follow-ups. Participants will also complete two brief questionnaires before each of the 5 lessons.

**Stat considerations**: With respect to power, a sample size of 15 is sufficient (power at 80%, and alpha at 0.05) to detect pre-post within group differences in effect size of 0.7, which is considered the minimum based on our previous studies.

Analyses will be conducted using parametric techniques and intention-to-treat and completer models.

**Duration of the Study:** 12 months

TABLE OF CONTENTs PAGE

1. BACKGROUND 5

1.1 Disease Background 5

1.2 Rationale for Performing the Study 5

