## Rationale for Performing the Study

Internet-delivery of CBT (iCBT) is one strategy for improving access to evidence-based treatment for anxiety disorders [2-4]. The CI and his team have now completed 30 trials of iCBT with more than 2200 Australian adults with depression and anxiety disorders. All trials have resulted in clinical outcomes at least comparable to those obtained from good face-to-face treatments, with high levels of acceptability to consumers. The Mental Health Association (MHA), NSW, provides education, advocacy, and support to consumers with anxiety. They would like to assist consumers to access evidence-based resources.

The planned project is a collaboration between the MHA and eCentreClinic at the Centre for Emotional Health (CEH), Macquarie University. This initial study will examine the feasibility of the MHA administering the online interventions developed at the eCentreClinic. This will be achieved through this initial trial, which utilises an open-trial design with a small number of participants (n=20), who will be recruited and managed by an MHA Psychologist, using software and an online course developed by the eCentreclinic.

**Outcome Measures:** Primary and secondary outcome measures will be administered.

The primary outcome measure is:

- Generalized Anxiety Disorder-7 Item Scale (GAD-7) [5]: Measures general symptoms of anxiety. The GAD-7 is sensitive to symptoms of anxiety disorders.

The secondary outcome measures are:

- Patient Health Questionnaire-9 Item (PHQ-9) [6]: Measures symptoms of major depressive disorder.
- Kessler 10-Item (K-10) [7]. Measures symptoms of psychological distress.
- Treatment satisfaction measures [developed by the researchers]: Measures satisfaction with treatment.
- The Things You Do Questionnaire [developed by the researchers]: Measures frequency of adaptive behaviours performed by a participant in the previous week.

In addition, the GAD-7 and PHQ-9 will be administered at the beginning of each lesson to monitor anxiety and mood.

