# Study OUTLINE

## Study Flow Table

| **Dates** | **Phase** | **Activities** |
| --- | --- | --- |
| June-July 2012 | Recruitment | Eligible applicants recruited by MHA |
| August 2012 | Intervention | Participants begin intervention (8 week Course).  Complete outcome questionnaires at pre-intervention  Complete GAD-7 and PHQ-9 before each lesson  Weekly contact from MHA Psychologist |
| October | Post-Intervention | Participants complete intervention.  Complete outcome questionnaires at post-intervention  Telephone feedback from MHA Psychologist |
| December | 2-month follow-up | Complete outcome questionnaires at 2-month follow-up  Telephone feedback from MHA Psychologist |
| February | Write-up | Write up of results and submission of manuscript for publication |
| May | Project Close-Out | Submit final report to MQ HREC  Submit reports to MHA and eCentreClinic |

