## Investigation plan

An open trial, with 1 group (n=20).

This design tests the short and medium term efficacy of the online eCentreClinic Wellbeing Course to MHA consumers, when administered by the MHA.

MHA consumers aged 18-64 years who telephone the [name] Anxiety Support line, will be informed about the aims of the study, and invited to apply. Those interest will be provided with more information and then sent an informed consent form, and asked to complete and return this. Those who complete the form will be telephoned by a Psychologist at the MHA who will provide more details, and administer the Patient Health Questionnaire-9 Item and Generalised Anxiety Disorder-7 item questionnaires. Applicants with scores too high or too low on these questionnaires will be automatically excluded with clear information about where to get treatment, while eligible applicants will be asked to provide demographic details and contact details for their GP.

Eligible applicants will receive an email confirming their participation and start date of the course. On the start date they will receive login codes and instructions to begin the 8-week course. The first part of the first lesson includes standardized questionnaires of anxiety, depression and disability. Course content includes evidence-based principles of managing anxiety and depression. Each of the five lessons contains a printable homework assignment designed to reinforce the material in the lessons. Participants will receive weekly telephone calls or emails from trained and supervised clinical staff at the MHA who will provide support, encouragement and will answer questions about the content of the Course.

Participants will be encourage to log at least weekly to review course materials. They will be asked to complete the GAD-7 and PHQ-9 before each lesson and all questionnaires at week 9 (i.e., at post-education) and again at 2 month follow up. At post-treatment and follow up, participants will receive a telephone call from the MHA Psychologist summarising their individual results. Post 2-months, they will be emailed a summary of the overall results, will be invited to request copies of any published articles when they become available and will be provided information about how to access further treatment should they want it.

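### Section 6.3 rests risk monitoring on weekly GAD-7 and PHQ-9, but the schedule gives five lesson-linked readings in eight weeks, and no stated in-course trigger uses question 9

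*Protocol*

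**What the plan says.** **Frequency in the safety section.** Protocol section 6.3 (Participant safety) makes the statement twice: "During the trial participants will complete a weekly measure of anxiety symptoms (GAD-7) and depression (PHQ-9"), and "Risk will be monitored through the weekly administration of reliable outcome measures which will monitor symptoms of depression and suicidality".

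**Frequency in the schedule.** The other sections link the in-course readings to lessons:
- Summary: "Participants will also complete two brief questionnaires before each of the 5 lessons".
- Section 1.2 (Rationale): "the GAD-7 and PHQ-9 will be administered at the beginning of each lesson to monitor anxiety and mood".
- Section 5.1 (Study Flow Table): "Complete GAD-7 and PHQ-9 before each lesson".
- Section 5.2 (Investigation plan): "They will be asked to complete the GAD-7 and PHQ-9 before each lesson and all questionnaires at week 9". The same section spreads the five lessons over eight weeks.
- Section 5.3 (Study Procedure risks) places the PHQ-9 at pre-treatment, before each of the five lessons, at post-treatment and at the 2-month follow-up.

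**In-course contact triggers.** Section 5.3 has one numeric rule, a PHQ-9 rise of at least 5. Section 6.3 adds contact when symptoms clearly worsen or fail to improve, and then: "Significant deterioration in mood or elevated distress triggers protocols involving the MHA Psychologist contacting the participant". Follow-up is left to a clinic policy that is cited but not shown.

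**Question 9.** A threshold (score above 1) appears in the Safety Assessment of the appendix telephone interview, which is written for applicants.

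**Other contact.** Section 5.2: "Participants will receive weekly telephone calls or emails from trained and supervised clinical staff at the MHA who will provide support, encouragement", and answers to questions about course content.

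**The concern.** The safety section claims a property, weekly measurement of mood and suicidality, that the schedule cannot deliver. The timing matters because section 5.3 itself warns that practising the techniques often raises symptoms in the short term. Readings also depend on engagement: a person who stops opening lessons stops producing scores, and section 5.2 only encourages a weekly log-in.

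The second part concerns use of the data. Section 6.3 says the measures monitor suicidality. The PHQ-9 item on thoughts of death or self-harm has a threshold at screening, yet no stated in-course trigger refers to it, so the suicidality claim has no item-level rule behind it once a participant is enrolled.

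What is at stake is safety conduct in a 20-person open trial. The estimate of pre-post change on the GAD-7 does not depend on it. How often to measure and when to make contact are matters for the protocol, and would not normally be left to a statistical analysis plan.

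**Working it through.** **Inputs.** Course length 8 weeks and 5 lessons (section 5.2); 20 participants (section 3.3); one in-course reading per lesson (Summary, 1.2, 5.1, 5.2, 5.3). The protocol states no coverage figure to reproduce.

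**Coverage of weeks.**
- Most weeks with a reading: 5, reached when the five lessons fall in five different weeks. 5/8 = 62.5%.
- Fewest weeks without one: 8 - 5 = 3. 3/8 = 37.5%.
- For 20 participants: 20 x 3 = 60 of 20 x 8 = 160 participant-weeks.

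These are lower bounds on the gap. The confirmation email in the appendix gives access to all materials from the start, so two or more lessons may be opened in one week.

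**Do the full assessments fill the gap?** No. The pre-treatment set is in the first part of lesson 1 (section 5.2) and has to be completed to enter the course, so it coincides with the lesson 1 reading. The post-treatment set is at week 9, after the eight weeks. A participant who stops opening lessons and does not withdraw therefore has no reading between the last lesson opened and week 9.

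**Can a rise in question 9 escape the stated triggers?** Assume items are scored 0 to 3. Let question 9 rise by q and the other eight items fall by r in total, so the change in the PHQ-9 total is q - r. A move from 0 to 2 or 3 crosses the screening threshold, with q = 2 or 3.
- If r = 0, the total rises by 2 or 3. That is below 5, so the numeric rule is silent. The total has not improved, however, so on a plain reading the failure-to-improve trigger applies.
- If r is greater than q (at least 3 when q = 2, at least 4 when q = 3), the total falls. The numeric rule is not met, and on the total the participant has improved. Only the undefined elevated-distress trigger, or something in the clinic policy that is not shown, would lead to contact.

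The second pattern is the real gap in the stated rules: overall improvement with a worsening suicidality item.

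**The case against.** The best opposing case is that this is a wording slip with small consequences. None of the schedule sections says that the scales are given only before lessons, so the text shows an inconsistency and does not settle which version operates. Replacing the weekly wording in two sentences would remove it. The trial excludes severe depression and suicidal intent or plan, has weekly psychologist contact and weekly team meetings, gives crisis details in email footers, and follows detected deterioration with a telephone risk assessment. Section 6.5 (Early termination) covers withdrawal: supervision by the psychologist, an invitation to report symptoms, contact after deterioration, and consent to contact the GP. The risk assessment form is headed for applicants and participants, so it may be used in-course, and the clinic policy may contain a cut-off.

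Most of this stands and limits the point. Three stronger readings that a reader might infer are not supported:
- **That nobody is required to ask about mood in a week without a reading.** Section 6.3 does require weekly measurement; the difficulty is that the schedule does not provide it.
- **That the attrition allowance makes coverage worse still.** Section 8.1 does not say that those lost stop opening lessons, and for those who withdraw section 6.5 applies.
- **That any isolated rise in question 9 goes unnoticed, or that the GAD-7 needs its own cut-off.** The failure-to-improve trigger covers a PHQ-9 total that rises by 2 or 3, and section 6.3 applies it to anxiety as well as depression.

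What the objection does not answer is this. Five readings are not weekly whatever the clinic policy says. The weekly contact may be an email and is described as support and content help, with no stated risk check. Rewording alone would also leave suicidality monitoring with no item-level rule.

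**Conclusion.** The point holds and should be fixed, as a matter of safety conduct. Section 6.3 promises weekly readings, while the schedule gives at most five in eight weeks: at least 3 of 8 weeks per participant, or 60 of 160 participant-weeks, without one. That size assumes the lesson-linked schedule operates, as the Summary and sections 1.2, 5.1, 5.2 and 5.3 all indicate, and that every participant opens all five lessons in different weeks. It is the most favourable case under that schedule.

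Separately, no stated in-course trigger refers to question 9. A participant whose question 9 score rises while the PHQ-9 total falls meets neither the 5-point rule nor the failure-to-improve trigger. This rests on 0 to 3 item scoring and on the protocol text alone, since the clinic policy is not shown. The other safeguards reduce the gap without closing it.

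**What to change.** **(a) Make section 6.3 and the schedule agree**, in one of two ways:
- Keep weekly measurement, and prompt the PHQ-9 and GAD-7 through the existing weekly email in any week without a lesson reading.
- Replace the weekly wording with before-each-lesson wording in both sentences of section 6.3, and add a brief mood and risk question to the existing weekly psychologist contact in weeks without a reading.

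**(b) Add a question 9 trigger.** State in sections 5.3 and 6.3 that a question 9 score above 1 at any in-course reading leads to the same psychologist contact as a PHQ-9 rise of 5. Staff already use this value at screening, where it opens further safety questions, and the item is already collected.

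**Cost.** The first option under (a) adds readings of 9 + 7 = 16 items. For participants who open all five lessons this is at least 8 - 5 = 3 each (20 x 3 = 60) and at most 8 - 1 = 7 each (20 x 7 = 140), the latter if all lessons are opened in one week. This runs against the aim in the confirmation email of keeping questionnaires few, and a prompt does not guarantee a reply. The second option adds no questionnaires, only a short question in at least 3 weeks per participant. Part (b) needs no new data. Both parts bring somewhat more psychologist calls.

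### The protocol says its repeated questionnaires monitor suicidality, but its only numeric in-trial contact trigger cannot be reached by PHQ-9 question 9 alone

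*Protocol*

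**What the plan says.** Participant safety states that risk will be monitored by weekly use of "reliable outcome measures which will monitor symptoms of depression and suicidality as well as symptoms of anxiety".

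For enrolled participants the protocol gives these grounds for contact:

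- **Numeric.** Study Procedure risks says of the PHQ-9: "An increase of 5 or more points is considered an indicator of deterioration, and if this occurs, it will trigger telephone and email contact". After that, "a Psychologist will make 3 attempts to co-ordinate a telephone assessment to determine risk and develop a management plan".
- **Not numeric.** Participant safety adds: "If symptoms significantly deteriorate or do not improve, the individual will be contacted as soon as possible by the MHA Psychologist". It also says: "Significant deterioration in mood or elevated distress triggers protocols involving the MHA Psychologist contacting the participant to discuss their emotional state". Neither statement defines its terms. Follow-up is to go by an eCentreClinic policy that is not reproduced.
- **General.** MHA staff telephone or email participants every week (Investigation plan). The Psychologist may contact the GP if sufficiently concerned, and "Members of the research team will meet at least weekly to discuss progress" (both Study Procedure risks).

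Question 9 has its own cut in one place, the Safety Assessment in the telephone interview appendix. There, a score above 1 leads to safety questions (a) to (d), and a yes to (c) or (d) leads to exclusion and a risk assessment. That text is addressed to applicants. The Risk Assessment form that follows is headed for participants as well, but the protocol does not say which in-trial answer opens it.

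**The concern.** The protocol treats question 9 as its suicidality item at entry and repeats the PHQ-9 through the trial. It then attaches its only in-trial number to a rise in PHQ-9 points and names no item. A new report of suicidal thoughts is a change in one item, and a rule on the total responds poorly to that.

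What is at stake is a prompt risk contact. Study Procedure risks bars applicants at risk of suicide or self-harm because "they require more immediate and intense support than can be provided via the Internet". The same reasoning applies to a participant who becomes at risk after enrolment. The section also warns that practising the techniques can raise symptoms: "in the short term, this often leads to an increase in levels of symptoms". A clinician without a fixed rule could therefore read a worse answer as an expected effect.

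Forms are completed on the eCentreClinic website. Under Storage and archiving, eCentreClinic investigators see non-identified data, while the MHA Psychologist can identify participants. The protocol does not say who reads individual item scores, so a written flag matters more.

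**Working it through.** The 5-point trigger is a stated rule, not a calculated figure, so there is nothing to reproduce. The check is range arithmetic.

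**Inputs**

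- Trigger: PHQ-9 rise of at least 5 (Study Procedure risks), read as the total score because no item is named. The rule does not say which earlier form the rise is counted from. The arithmetic is the same for any reference form.
- Item range: 0 to 3, assumed.
- Entry cut on question 9: above 1 (Safety Assessment).

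**Is the assumed range consistent with the protocol?** With nine items of equal range, the largest total is 9 × item maximum. The protocol uses depression cut-offs of above 22 (Exclusion criteria) and above 23 (Study Procedure risks), so totals above 23 must be possible.

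| Item maximum | Largest total | Can exceed 23? | Largest rise of one item | Reaches +5? |
|---|---|---|---|---|
| 1 | 9 | no | 1 | no |
| 2 | 18 | no | 2 | no |
| 3 | 27 | yes | 3 | no |
| 4 | 36 | yes | 4 | no |
| 5 | 45 | yes | 5 | yes |

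Maxima of 1 and 2 are ruled out. The conclusion holds for 3 (assumed) and also for 4.

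**Question 9 alone.** Let r be the rise on question 9 and d the net change on the other eight items. The trigger fires when r + d ≥ 5. With d = 0 the largest change is 3, and 5 − 3 = 2 points short.

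**Help needed from the other items.** The condition is d ≥ 5 − r:

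- r = 1: d ≥ 4
- r = 2: d ≥ 3
- r = 3: d ≥ 2

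**Masking.** Suppose the total is 12 with question 9 at 0 and the other items at 12. On a later form question 9 is 2 and the other items are 9, so the total is 11. The change is 2 + (9 − 12) = −1, which is 5 − (−1) = 6 points below the trigger. The entry cut would flag this form, because 2 is above 1.

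**Number of forms an item rule would cover**

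- Before each lesson (Study Procedure risks): pre + 5 lessons + week 9 + 2 months = 8 per person, or 7 if the pre-treatment set is the lesson 1 form.
- Weekly (Participant safety): 8 + week 9 + 2 months = 10, or 11 with a separate pre-treatment set.
- If all 20 complete everything: 20 × 7 = 140 to 20 × 11 = 220.
- If 15 complete 7 each: 15 × 7 = 105, and fewer with dropout.

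**The case against.** The strongest reply is that this is an absence and not an error. The PHQ-9 contains the item and is given repeatedly, so the statement that suicidality is monitored is true as far as it goes. The 5-point rule is called an indicator of deterioration, not the suicidality rule or the sole ground for contact. The wording in Participant safety is broad: the masked example could count as failure to improve or as elevated distress. A registered Psychologist trained to manage risk is in weekly contact with a group of only 20, and the eCentreClinic policy may already hold an item rule.

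Much of this stands. A reader might infer that a participant who newly reports suicidal thoughts would get no response, or that the two safety sections contradict each other. The documents support neither reading. Several routes could lead to contact, and the unseen policy may add another.

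A reader might also infer from the comma between the total-score and question-9 conditions in the Safety Assessment that the entry cut is unclear. The script line just below joins depressive symptoms and thoughts of being better off dead with an or, which largely settles that question 9 is enough by itself.

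The reply does not supply a stated rule. Every route it names either depends on someone noticing the item and judging it, or lies outside this protocol. Contact triggers are a safety procedure, so this is not a matter a protocol would leave to a statistical analysis plan.

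**Conclusion.** The point holds, limited to what this protocol states. The only numeric in-trial trigger cannot be met by question 9 alone: the largest rise is 3 against a required 5. A fall on other items can hide any rise on question 9. The explicit cut on that item is not carried past telephone screening. Detection of a new report of suicidal thoughts therefore rests on discretion or on rules not shown here.

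This rests on reading the trigger as a change in the total and on items scored 0 to 3. A 0 to 4 range gives the same conclusion. The documents give no frequency for such answers, so no number of missed cases is claimed. The finding is a missing explicit rule, not missing care, and it affects neither the sample size nor the analysis. It should be corrected because the safeguard concerns suicide risk and most of what it needs is already in the protocol.

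**What to change.** Add to Study Procedure risks, beside the 5-point rule: *On any in-trial PHQ-9, including post-treatment and follow-up, a question-9 score above 1 is sufficient by itself to trigger Psychologist contact and safety questions (a) to (d), whatever the total score. A yes to (c) or (d) leads to the Risk Assessment form and documented management or referral, not exclusion.* Cross-refer to this in Participant safety. If the eCentreClinic policy already contains such a rule, cite it there instead.

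A further trigger for any rise in question 9 would catch a change from 0 to 1. It is stricter than the entry cut and is optional. The look-back periods in the safety questions need not change to close the gap.

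The cost is a short paragraph, a cross-reference and an item-level check of the online forms, for which someone must be named. That is at most about 140 to 220 forms with full completion by 20 participants, or about 105 if 15 complete 7 each. Each 1% of forms meeting the rule means about 1.4 to 2.2 calls (0.01 × 140 to 0.01 × 220) with full completion. Some calls would concern a stable score already known from entry. The item, the cut, the staff and the form already exist.
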